#### Statistical analysis

A descriptive statistical analysis will be performed for all study variables. We will calculate the mean, median, and standard deviation for quantitative variables, and the absolute and relative frequency for qualitative variables. We will use SPSS 19.0 (SPSS Inc., Chicago, Illinois, United States) to analyze the data statistically. An intention-to-treat analysis will be applied using the last observation carried forward method for missing data. Analysis of covariance with the baseline as the covariate will be used to assess differences in treatment outcomes between the two groups at each of the time points. To correct for an inflated risk of type 1 errors, multiple comparison procedures suggested by Ludbrook et al. [14] will be used for the outcome measure by using it as a covariate in the statistical analysis. A data safety monitoring board has been established to assess the progress of the trial, particularly the safety endpoints.

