### Randomization

Participants who meet the inclusion criteria and sign the informed consent form will be allocated to a group (Fig. 1). A stratified and block randomization design has been adopted. There are two groups and the distribution ratio is 1:1. The block size is six. Patients are stratified at the time of study entry by study center. Allocation is based on random numbers from 1 to 198 generated by SAS 9.2 and saved in a sealed envelope by an independent clinical statistician. In a clinical emergency, the individual’s randomization code and group allocation can be quickly identified by checking the envelope. The randomization design is provided by the Jiangsu Famous Medical Technology Co., Ltd.

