##### SOFA questionnaire

The clinical symptom questionnaire for SCAP will be assessed at baseline, and at days 0, 4, 7, 14, and 28 of the treatment phase.

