#### Sample size considerations

This study is designed to show the superiority of the TCM group compared to placebo treatment. Our primary hypothesis is that adjunct TCM treatment in patients with SCAP will result in reduced treatment failure compared to the placebo. To estimate the frequency of our primary endpoint, we used data for SCAP patients from completed studies [12]. Based on these previous trials, we assumed a treatment failure rate of 30% in the placebo group and 10% in the adjunct TCM group over 28 days. Thus, a sample size of 198 patients is needed to achieve a statistical power of 90% (two-sided type-1 error of 5% in both scenarios). We intend to recruit 198 study patients from July 2017 to December 2019.

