#### Intention-to-treat and per-protocol population

Following the intention-to-treat principle, all patients receiving at least one dose of study medication will be included in the analysis with group allocation as randomized. Patients found to have violated the inclusion criteria or met the exclusion criteria due to information that was not available at study entry will be excluded post randomization. Criteria for excluding patients from the per-protocol analysis are, in addition, withdrawal of informed consent or non-compliance with the study medication or the concomitant procedures. Therefore, patients stopping or pausing the study medication at any time will not be considered in the per-protocol analysis. A patient will not be followed up for any study measure if they withdraw informed consent. In all other cases, the follow-up will be performed as planned.

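### Last observation carried forward, the only missing-data method named, generally counts patients lost before an event as successes on the primary endpoint and is not limited by endpoint

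*Protocol article*

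**What the plan says.** The protocol article, under Statistical analysis, gives one sentence on missing data: "An intention-to-treat analysis will be applied using the last observation carried forward method for missing data". It makes no exception for the binary primary endpoint, for death or for any other reason a value may be absent. The next sentence describes the comparison of outcomes: "Analysis of covariance with the baseline as the covariate will be used to assess differences in treatment outcomes between the two groups at each of" (it goes on to name the assessment times).

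The primary outcome is treatment failure, early (up to 72 h) or late. It is met by events such as new invasive ventilation or death, by radiographic progression, or by persistent severe respiratory failure. Sample size considerations set the horizon: "we assumed a treatment failure rate of 30% in the placebo group and 10% in the adjunct TCM group over 28 days".

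On who can be lost, the section on the intention-to-treat and per-protocol populations keeps anyone with at least one dose in the analysis and says: "A patient will not be followed up for any study measure if they withdraw informed consent". It then says that follow-up continues as planned in all other cases. The adverse event section adds that dropouts are not replaced.

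SOFA "will be assessed at baseline, and at days 0, 4, 7, 14, and 28 of the treatment phase". CAP-CRO runs on to days 30, 60 and 90. Neither section says what value a patient has after death.

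**The concern.** Carrying the last value forward assumes that a patient's state stays where it was last seen. For an endpoint that accumulates over 28 days, the last state of someone who leaves before an event is, with few exceptions, that failure has not yet happened. The method turns this into a definite success and leaves out the risk over the remaining days. The recorded failure rate is then too low in each arm, by an amount that depends on how many were lost and how sick they were. If these differ between arms, the comparison is biased, in either direction.

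Such losses are foreseeable here. Consent withdrawal ends all measurement. Patients too ill to consent enter on their next of kin's consent and are asked for their own later, so refusal at that point may depend on prognosis. The trial is single-blind, which gives no assurance that loss will be equal.

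For the scores, a patient who dies has no later measurements. If these count as missing data, the stated rule fills them with a value recorded in life.

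**Working it through.** **Inputs from the protocol article.** Failure 30% on placebo and 10% on TCM over 28 days; "two-sided type-1 error of 5% in both scenarios"; power 90%; 198 patients; "There are two groups and the distribution ratio is 1:1", hence 99 per arm. **Inputs assumed.** The loss shares and the failure risk among those lost; the article states neither.

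**1. The plan's own figure.** With the pooled two-proportion formula,

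n = [1.96·√(2·0.20·0.80) + 1.2816·√(0.30·0.70 + 0.10·0.90)]² / 0.20² = 82 per arm (164 in total), or 92 per arm (184) with continuity correction.

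Neither gives 198. At 99 per arm the power for 30% vs 10% is 94.6%. The stated number is therefore more than these inputs need; that is a separate matter and does not drive this point.

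**2. Recorded rate under the stated rule.** Let p be the true failure rate, L the share of the arm lost before failing, and f the share of those lost who would have failed by day 28. Then

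recorded rate = p − L·f.

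**3. Equal loss, average risk among the lost (f = p), true 30% vs 10%, 99 per arm.** The recorded rate is p(1 − L).

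| Loss in each arm | Recorded rates | Difference (points) | Power |
|---|---|---|---|
| 0% | 30% vs 10% | 20 | 94.6% |
| 5% | 28.5% vs 9.5% | 19 | 93.2% |
| 10% | 27% vs 9% | 18 | 91.5% |
| 20% | 24% vs 8% | 16 | 87.2% |

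**4. Unequal loss, true 30% in both arms, control losing 5%.** The false difference, in favour of TCM, is f × (L in TCM − L in control). The error is the two-sided rejection rate of an unadjusted two-proportion test at 99 per arm.

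| Loss in TCM | f | Recorded, control vs TCM | False difference (points) | Two-sided error |
|---|---|---|---|---|
| 10% | 0.3 | 28.5% vs 27.0% | 1.5 | 5.6% |
| 10% | 0.6 | 27.0% vs 24.0% | 3.0 | 7.7% |
| 15% | 0.5 | 27.5% vs 22.5% | 5.0 | about 13% |
| 20% | 0.3 | 28.5% vs 24.0% | 4.5 | 11% |
| 20% | 0.6 | 27.0% vs 18.0% | 9.0 | 33% |

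Third row in full: control 0.30 − 0.05·0.5 = 0.275; TCM 0.30 − 0.15·0.5 = 0.225.

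**5. The other direction.** True 30% vs 10%, control losing 20% and TCM 5%, average risk among the lost: 0.30·0.80 = 24% vs 0.10·0.95 = 9.5%. The difference is 14.5 points and the power 78%.

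**6. Scores.** Suppose a patient dies on day 5 after a day-4 assessment. Read literally, the rule puts the day-4 CAP-CRO value at days 7, 14, 21, 28, 30, 60 and 90 (seven time points) and the day-4 SOFA value at days 7, 14 and 28 (three).

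**The case against.** The strongest reply is that little will be missing. Follow-up stops only on consent withdrawal, inpatients are reassessed every 24 h, and telephone interviews at days 30, 60 and 90 have the primary-care physician as back-up. Shock, new ventilation and death mostly occur where they will be seen. Under equal loss of 5% to 10% the difference shrinks only to 19 or 18 points, power stays above 90%, and the bias is conservative. All of this stands. It limits the likely size, but does not make the rule suitable: nothing in the article ensures that loss is small or balanced.

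A reader might infer more than the article supports:

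- **That every early loss becomes a success.** A patient lost while in severe respiratory failure might be carried forward as a failure, those lost after failing stay failures, and some early leavers may be removed under the post-randomization exclusion rule.
- **That deaths are hidden.** An observed death counts as failure in the primary endpoint, and all-cause mortality is reported separately. The article does not say that scores after death are treated as missing data; this is inferred from the lack of any other rule.
- **That discharged patients are frozen at an early value.** Assessment continues after discharge, so the rule acts only when a scheduled value is actually missed.
- **That standard errors are always too small.** Carrying scores forward can raise or lower the variance, and no calculation here settles which.
- **That equal loss is harmless when there is no true effect.** This also requires those lost to carry the same failure risk in both arms.

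A separate analysis plan may add sensitivity analyses, and their absence from the article is no fault. The point is the method that the article does fix.

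**Conclusion.** The point holds in this form: the article fixes a single missing-data method for all endpoints, and it is unsuitable for a cumulative failure endpoint. The mechanism follows from the text. Its size cannot be known, because no dropout rate is given. Over the assumed range, equal loss of 5% to 20% shrinks the planned 20 points to between 19 and 16. With 5% loss in control and 10% to 20% in TCM, the false difference is 1.5 to 9 points and the two-sided error 5.6% to 33%. Heavier loss in control works against TCM. These figures are illustrations, not predictions; the true effect on the primary result may be modest. The problem with scores after death is secondary and rests on reading the sentence literally.

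**What to change.** Delete last observation carried forward.

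- **Primary endpoint.** Establish status to day 28 from all available hospital and follow-up information. Telephone contact can supply deaths and perhaps ventilation, but it cannot establish radiographic progression or the oxygenation criterion, and it cannot reach patients who have withdrawn consent. Impute the statuses that remain unknown by multiple imputation, with a sparse model of arm and baseline severity. Avoid centre-by-arm cells: with 11 centres and about 10 expected TCM failures (0.10 × 99 = 9.9) they would be too thin. Add a sensitivity analysis that counts unknowns as failures, or a tipping-point analysis. In the 5% vs 15% illustration, counting unknowns as failures gives 27.5 + 5 = 32.5% for control and 22.5 + 15 = 37.5% for TCM. The sign of the difference reverses, which shows how far the conclusion would depend on the missing statuses.
- **SOFA and CAP-CRO.** Use a likelihood-based repeated-measures model for values missing in living patients, and state explicitly how death enters, for example ranked worst or as part of a composite.

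The cost is revised wording, some extra programming and slightly wider intervals. The design does not change, and the article reports 16 patients recruited at submission.

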### Outcome measures

#### Primary outcome measure

The primary endpoint is treatment failure, which includes treatment failure that occurred early or late. Early treatment failure is defined as clinical deterioration within 72 h of treatment (including shock, need for invasive mechanical ventilation not present at baseline, or death). Late treatment failure is defined as radiographic progression (increase of ≥50% of pulmonary infiltrates compared with baseline), persistence of severe respiratory failure (ratio of PaO_2_ to fraction of inspired oxygen < 200 mmHg with respiratory rate ≥ 30 breaths/min in patients not intubated), need for invasive mechanical ventilation not present at baseline, or death 72 h after treatment initiation. These criteria have been used previously with modifications [12].

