##### Length of hospital stay

The time to the earliest possible hospital discharge (days) is based on objective criteria (able to take food, liquids, and drugs orally; vital signs stable for > 24 h; recovered from CAP-related worsening of mental status; and no evidence of an acute serious CAP-related comorbidity that necessitates hospitalization). This endpoint will minimize any potential bias due to extended hospitalization for non-disease-specific reasons (a request from the patient or their relatives, lack of adequate home care, inability to transfer to a nursing home, or lack of assurance about compliance with treatment) [13].

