## Discussion

Despite advances in treatments with antimicrobial agents, mortality among hospitalized patients with SCAP is still high. SCAP remains the leading cause of death in the world [15]. TCM have been used for thousands of years in China for treating pneumonia, and it is widely used in many countries. Evidence from both clinicians and patients suggests that TCM may improve SCAP survival rates. However, the available evidence has been derived from only a few small randomized controlled trials.

Some studies have shown that TCM may have a beneficial effect on patients with CAP, including those with severe pneumonia [16]. In these patients, reviews show that TCM may reduce either length of hospital stay or mortality without causing complications [17]. However, insufficient data on SCAP are available, and the treatment in some studies was not according to syndrome differentiation. In view of these findings, a large prospective and adequately powered trial should conclusively determine the risks and benefits of adding TCM according to syndrome differentiation to the treatment of patients with SCAP.

In the current trial, we will include SCAP (risk class V in the pneumonia severity index) requiring hospitalization. According to previous studies, our study may not be powered to show a survival benefit. Our primary endpoint will be the rate of treatment failure, which includes treatment failure that occurred early or late. These criteria have been used previously with modifications.

Our secondary endpoints will be time to clinical stability, as defined by the guidelines of the Infectious Diseases Society of America and the American Thoracic Society, as well as length of intensive care unit and hospital stays, and in-hospital mortality.

In our study, we will administer an oral TCM granule for 28 days. All patients will be treated with antibiotics according to international guidelines. The treatment group will receive TCM according to the TCM syndrome. The control group will receive TCM placebo according to the TCM syndrome. Because a variety of treatment options have been adopted, we use the single blind method. We opted for an oral formula, since by choosing a uniform application formula, further bias can be prevented. Furthermore, the use of the placebo ensures the blinded design of this trial. Strict randomization will be implemented to minimize selection and evaluation bias.

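### The only comparative method stated, ANCOVA on the baseline value at each time point, suits the repeated scores but not the yes/no primary endpoint or the two time-to-event secondaries, and it leaves out centre

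*Protocol article*

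**What the plan says.** The Statistical analysis section of the protocol article lists descriptive summaries, the software, last observation carried forward for missing data, and one method for comparing the arms: "Analysis of covariance with the baseline as the covariate will be used to assess differences in treatment outcomes between the two groups". The sentence goes on to apply this at each time point and excepts no outcome. The multiplicity sentence that follows names no test. Read literally, it enters the outcome measure itself as a covariate, so it offers no alternative.

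The outcomes are of several kinds:

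- **Primary.** Under Primary outcome measure: "The primary endpoint is treatment failure, which includes treatment failure that occurred early or late". The Discussion calls it a rate: "Our primary endpoint will be the rate of treatment failure". Under Sample size considerations: "we assumed a treatment failure rate of 30% in the placebo group and 10% in the adjunct TCM group over 28 days".
- **Secondary, times.** These are time to clinical stability and length of stay. The latter is defined as "The time to the earliest possible hospital discharge (days) is based on objective criteria".
- **Secondary, binary.** All-cause mortality at 28 days and 3 months.
- **Secondary, repeated scores.** SOFA and CAP-CRO, each with a baseline and several later assessments.

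The Randomization section states: "Patients are stratified at the time of study entry by study center". Study setting and participants gives 11 hospitals. The analysis text names no centre term.

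**The concern.** ANCOVA with a baseline covariate needs an outcome that is measured before treatment and again afterwards. Treatment failure is not measured in that way. It is reached once or not at all, and it counts events after treatment begins, such as "need for invasive mechanical ventilation not present at baseline, or death". Nobody can have failed treatment before it starts, so the outcome's own baseline is the same for everyone. The sample size compares two proportions, which is not the analysis then described.

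The two time outcomes have no baseline value either, and a patient who dies first has no value at all. A comparison of means cannot represent that.

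At stake is pre-specification of the main result. No risk difference, risk ratio or odds ratio is named, so the article's text leaves the primary test and effect measure to be chosen later in a trial described as single-blind. The choice matters somewhat: at 99 per arm and 30% versus 10%, Pearson chi-square has 95.4% power and Fisher's exact test 93.2%.

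**Working it through.** **1. The plan's own figure.** Inputs from Sample size considerations are 30% versus 10%, with "a sample size of 198 patients is needed to achieve a statistical power of 90% (two-sided type-1 error of 5% in both scenarios"). Allocation is 1:1. The two-proportion formula with pooled variance under the null, mean rate (0.30 + 0.10)/2 = 0.20, gives

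n per arm = [1.96·√(2·0.20·0.80) + 1.2816·√(0.30·0.70 + 0.10·0.90)]² / 0.20²
= [1.1087 + 0.7019]² / 0.04 = 81.96, rounded up to 82, or 164 in total.

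The stated 198 does not follow directly. An unstated 20% addition gives it: 82 × 1.2 = 98.4, rounded up to 99 per arm. That is a separate matter. What counts here is that the sizing rests on two proportions and that 99 per arm has power to spare: (0.20·√99 − 1.1087)/0.5477 = 1.61, so power is 94.6%.

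**2. ANCOVA applied literally to treatment failure.** With a constant covariate the model is y = a + b·arm, with y coded 0 or 1. The estimate of b is the difference in failure proportions, that is, the risk difference. The test is a two-sample t-test on 0/1 data:

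t = (difference in proportions) / √(s²·2/99), with s² = [99·p₁(1−p₁) + 99·p₂(1−p₂)]/196, where p₁ and p₂ are the observed failure proportions.

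Exact enumeration of the two binomials at 99 per arm gives:

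| Test | Type I error (common rate 10%, 20%, 30%) | Power, 30% vs 10% |
|---|---|---|
| Literal ANCOVA (t-test on 0/1) | 5.2%, 5.2%, 5.1% | 95.4% |
| Pearson chi-square | 5.2%, 5.2%, 5.1% | 95.4% |
| Fisher's exact | 2.8%, 3.3%, 3.5% | 93.2% |

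The first two rows agree throughout.

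**3. Leaving centre out.** With 11 centres, 198/11 = 18 patients each, 9 per arm. The between-centre SD of failure on the log-odds scale is not in the article, so 0, 0.5 and 1.0 are assumed. Simulation with 4,000 trials per scenario, chi-square ignoring centre against a centre-stratified Mantel-Haenszel test:

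| Assumed SD | Type I error, unstratified / stratified | Power at 30% vs 10%, unstratified / stratified |
|---|---|---|
| 0 | 4.8% / 4.6% | 96.0% / 95.7% |
| 0.5 | 4.7% / 5.0% | 95.3% / 95.5% |
| 1.0 | 3.8% / 5.2% | 92.7% / 94.1% |

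The Monte Carlo standard error is about √(0.05·0.95/4000) = 0.3 points. A larger run of 40,000 trials puts the unstratified type I error at about 4.6% for SD 0.5, falling to about 3.3% for SD 1.0. It puts the power loss at about 0.2 to 1.5 points. At SD 0 there is no effect beyond simulation noise.

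**4. The time outcomes.** No arithmetic is needed. Both are defined by reaching a state (stability, or fitness for discharge). Death before that state leaves the time undefined, and neither outcome has a pre-treatment value to serve as covariate.

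**The case against.** The strongest reply is that the ANCOVA sentence was meant only for outcomes with a baseline and repeated visits, and that the primary test is left to a fuller plan. That is a possible reading, and a journal article may condense. But the sentence speaks of treatment outcomes in general, excepts none, and is the only comparative method given. It is therefore a method stated too broadly, not just a detail left out. The possible reading does lower the severity.

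The reply is strongest on centre. Whether centre enters the model is often left to an analysis plan, and the article says nothing false about it. This is the weakest part of the point.

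Four stronger readings are tempting, and the documents do not support them:

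- *The plan cannot give a risk difference.* It can: step 2 shows that the literal coefficient is one, though unadjusted for centre. Frequencies of qualitative variables are also to be reported.
- *The primary test is invalid.* Type I error is 5.1–5.2% with centre effects absent and below 5% with them, so no material excess of false positives follows.
- *Ignoring centre costs 3 to 5 power points.* Losses of that size appear at 30% versus 15% with SDs of 0.8 to 1.0. The plan assumes 30% versus 10%.
- *A life-saving treatment will appear to lengthen stay.* If those who die are scored at 5 days and survivors at 14, cutting mortality from 20% to 10% moves mean stay from 0.2·5 + 0.8·14 = 12.2 to 0.1·5 + 0.9·14 = 13.1 days. All these inputs are assumed. The change is 0.1 × (14 − 5) = 0.9 days, and its sign depends on deaths being scored shorter than survivors' stays. The article does not say how deaths are scored, and only a secondary endpoint is affected.

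A plain chi-square or logistic regression would also meet the core objection. The stratified test is preferred because it matches the randomisation.

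**Conclusion.** The point holds: the stated method fits the continuous repeated scores but not the binary primary endpoint, the binary mortality outcome or the two time-to-event secondaries, and it omits the stratification factor. For the primary endpoint this is a fault of specification, not of error control. The literal analysis behaves like a Pearson chi-square. Omitting centre makes it mildly conservative (type I error about 4.6% to 3.3% for SD 0.5 to 1.0) and costs about 0.2 to 1.5 power points, with power above 90% at 198 patients. Those centre figures rest on the assumed SDs, equal centres of 18, the planned 30% versus 10%, and full data. The time-to-event mismatch follows from the definitions and needs no assumed figures. This should be fixed, but it does not by itself undermine the trial.

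**What to change.** Amend the Statistical analysis section to state, by type of outcome:

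- **Treatment failure by day 28** (the horizon used in the sample size): a centre-stratified comparison at two-sided 5%. For example, a Cochran-Mantel-Haenszel test with the Mantel-Haenszel risk difference and 95% CI, or logistic regression with centre. Name one as primary.
- **Time to clinical stability and time to dischargeable status:** time-to-event methods with death as a competing event.
- **Continuous scores:** keep ANCOVA on the baseline value, with centre added, and say that it applies to these only.

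The cost is wording. Centre is already recorded for randomisation, and no extra patients, visits or data are needed. The Trial status section reports 16 patients recruited at submission, so the change could still have been pre-specified at that stage.

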##### Community acquired pneumonia-clinician report outcome (CAP –CRO)

A CAP-specific disease activity score, daily function, and health state will be assessed at baseline, at days 4, 7, 14, 21, and 28, and at the follow-ups at 30, 60, and 90 days.

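### The stated way of applying the multiplicity correction, through a covariate, corrects nothing for the repeated secondary scores

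*Protocol article*

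**What the plan says.** The Statistical analysis section of the protocol article makes two linked statements about inference.

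- The model: "Analysis of covariance with the baseline as the covariate will be used to assess differences in treatment outcomes". The section has this comparison made "between the two groups at each of the time points".
- The error control: "To correct for an inflated risk of type 1 errors, multiple comparison procedures suggested by" a cited methods paper "will be used for the outcome measure by using it as a covariate in the statistical analysis".

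The article gives no adjusted significance level, test order or family of hypotheses. The procedure is identified only by the citation and by this account of how it is applied.

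The time points come from the outcome sections. SOFA "will be assessed at baseline, and at days 0, 4, 7, 14, and 28 of the treatment phase". CAP-CRO "will be assessed at baseline, at days 4, 7, 14, 21, and 28, and at the follow-ups at 30, 60, and 90 days".

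The sample size section sets one primary hypothesis, on treatment failure, with "statistical power of 90% (two-sided type-1 error of 5% in both scenarios".

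**The concern.** A multiple comparison procedure works on p-values or on the thresholds they are compared with. A covariate changes the model that produces each p-value, and every test is still judged at 5%. The sentence joins the two as if the covariate were the means of correction.

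The need for correction is real, because two scores are to be compared between groups at many visits. An analyst who follows the sentence could report secondary results as corrected for multiplicity when they are not. An analyst who takes the outcome measure to mean a post-baseline value would also adjust away part of what the trial is trying to estimate. This is an explicit statement of method, so it is not the kind of detail that an article may leave to the analysis plan.

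**Working it through.** The plan states no figure for error control, so there is none to reproduce. The sample size is used only for the arm size: 198 patients at 1:1, so 99 per arm.

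**Inputs from the article**
- SOFA: days 4, 7, 14 and 28, with day 0 taken as baseline. K = 4 tests.
- CAP-CRO: days 4, 7, 14, 21, 28, 30, 60 and 90. K = 8 tests.
- Significance level 0.05, two-sided.

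**Inputs assumed, because the article gives none**
- Correlations between visits of 0.3 to 0.8.
- A true effect of 0.5 SD at every visit, where an effect is needed.

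**Step 1. Size of the problem if nothing is corrected.** For independent tests, family-wise error = 1 − 0.95^K.
- K = 4: 1 − 0.95^4 = 18.5%.
- K = 8: 1 − 0.95^8 = 33.7%.
- K = 4 + 8 = 12: 1 − 0.95^12 = 46.0%.

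Visits on the same patients are correlated, which lowers these values. Simulating the 12 test statistics as multivariate normal gave 35%, 28% and 23% for within-scale correlations of 0.5, 0.7 and 0.8. The result also depends on the correlation between the two scales. In a separate check it was 37%, 30% and 25% with the scales independent, and 32%, 27% and 23% with a between-scale correlation of 0.5.

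**Step 2. What the covariate clause does under each reading**

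| Covariate | Effect on type 1 error | Effect on the estimate |
|---|---|---|
| Baseline value of the outcome | None: repeats the model already given | None |
| Another post-baseline value of the outcome | None | Part of the treatment effect removed |
| The outcome being analysed | Model degenerate | Estimate exactly zero |

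**Step 3. Check on type 1 error.** Analyses of covariance were simulated with 99 per arm, 2,000 replicates, no true effect, and equal correlation ρ = 0.3, 0.5 or 0.7. The post-baseline covariate was the value at the preceding visit (for the first visit, the next one). The table shows the chance of at least one false positive.

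| Model | K = 4 | K = 8 |
|---|---|---|
| Baseline covariate only | 15.9–16.5% | 26.2–30.0% |
| Baseline plus a post-baseline value | 17.0–18.6% | 30.9–32.7% |
| Baseline covariate, tests at 0.05/K | 3.2–4.7% | 3.4–4.8% |

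Only the threshold adjustment controls the error. Holm starts at the same 0.05/K threshold, so with no true effect anywhere its result is identical.

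**Step 4. Check on the estimate, for the post-baseline reading only.** With equal correlation ρ, and baseline already in the model, the added covariate has coefficient (ρ − ρ²)/(1 − ρ²) = ρ/(1 + ρ). The effect that remains is δ × [1 − ρ/(1 + ρ)] = δ/(1 + ρ). With δ = 0.5 SD:
- ρ = 0.3: 0.5/1.3 = 0.385 SD, a loss of 23%.
- ρ = 0.5: 0.5/1.5 = 0.333 SD, a loss of 33%.
- ρ = 0.7: 0.5/1.7 = 0.294 SD, a loss of 41%.

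Simulation agreed to within 0.004 SD. Power per test fell from 95–99.9% to 77–84%. With baseline as the only covariate, the effect was recovered at 0.50 SD.

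**The case against.** The strongest reply is that the sentence does name multiple comparison procedures, by citation, and says they will be used. The covariate clause may be only a garbled description of a valid method. Neither the cited paper nor a full analysis plan is at hand, so it cannot be said that no correction will be made. This stands. A reader might infer that the trial has no error control at all, but the article supports only the narrower statement that the described way of applying it does not work.

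Second, the preceding sentence has already fixed the covariate as baseline, so the clause plausibly means the baseline value again. On that reading no treatment effect is lost. This stands too, and it makes the attenuation in Step 4 conditional on one reading. It does not rescue the clause, which would then be a repetition with no bearing on type 1 error.

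Third, a reader might infer that the primary result is at risk, through either inflated error or a diluted effect. The article does not support that. Treatment failure is one binary composite with no baseline value, tested under one hypothesis at two-sided 5%. The wording about covariance analysis at each time point fits the repeated scores, and nowhere does the article propose adjusting treatment failure for a post-baseline measure.

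Fourth, the article does not declare the 12 tests to be one confirmatory family, and 46% assumes both independence and no correction. That is fair. The figure is an upper marker, and the values under correlation are more realistic.

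**Conclusion.** The sentence is wrong as written, in a limited way. On none of the three readings does the covariate clause deliver the correction that the sentence announces. The consequence falls on the secondary SOFA and CAP-CRO comparisons. If the clause were all that was done, family-wise error over the 12 tests would be up to 46% with independence and about 23–35% under the assumed within-scale correlations. Taken one scale at a time, it would be about 16% for SOFA and 26–30% for CAP-CRO at assumed correlations of 0.3–0.7.

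Loss of treatment effect (23–41% under the assumed correlations) arises only if a post-baseline value is used as the covariate, which the article does not clearly say. The primary analysis is untouched. The wording should be corrected before analysis, but it does not endanger the trial's main conclusion.

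**What to change.** In the Statistical analysis section:

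1. Delete the clause that applies the procedure by way of a covariate.
2. State that only baseline values enter as covariates, and that no post-baseline variable is adjusted for in any treatment comparison.
3. Name the p-value or threshold adjustment (Holm, for example) and the set of repeated secondary comparisons it covers. Alternatively, state that these comparisons are unadjusted and descriptive.

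The cost is a few sentences. With Holm, secondary claims become somewhat harder to reach; with the descriptive option, they are not made as confirmatory claims. The sample size and primary test do not change. The Trial status section reports 16 of the planned 198 patients recruited at manuscript submission, so at that stage the change could have been made early.
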